#### 2) Methods

Toshiba Corporation will recruit volunteers from among its employees and obtain informed consent via electronic signature through a dedicated website. Each consenting participant will be automatically assigned a study ID. Toshiba will verify that the consenting individuals are valid employees with internal email addresses, confirm their genotype and blood pressure, and notify eligible individuals of their study ID and the URL for the urine test.

Spot urine analysis will be conducted by Healthcare Systems Co., Ltd. (HS), commissioned by Wellmira Inc. Participants will input their ID, name, address, email address, healthcare utilization status, and health awareness responses into a form accessed via the URL provided by Toshiba. HS will mail test kits for both pre- and post-intervention collection and conduct the initial urine analysis. HS will report the ID, email address, health awareness and medical visit survey responses, and test results to Wellmira. Wellmira will then report the ID, health awareness and medical visit responses, and urine submission status to Toshiba.

Toshiba will finalize participants based on urine submission and survey completion, and randomly assign them into the three groups. Toshiba will generate a participant list with IDs, allocation groups, and health check data from 2023 (sex, age, height, weight, systolic and diastolic blood pressure) and provide this to Wellmira.

Wellmira will inform participants in the intervention group that they carry a salt sensitivity genotype and request that they log every meal in the *CALOmama PLUS* app. Weekly columns and quizzes on salt sensitivity and salt reduction will be delivered via the app. Participants in control group 2 will be asked to record their meals using the app but will not receive genetic information or salt reduction content. The intervention period using *CALOmama PLUS* will last for 3 months.

At the end of the trial, Toshiba and Wellmira will instruct participants to submit post-intervention urine samples using the pre-mailed kits and complete a follow-up survey via a URL. Information collected will include ID, health awareness, age, weight, systolic and diastolic blood pressure (if measurable), and medical visit status. HS will report post-intervention urine test results to Wellmira and notify participants of their own pre- and post-test results.

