Wellmira will provide Kyoto University with anonymized data including participant ID, allocation group, sex, pre- and post-intervention urine test results, health awareness, age, height, weight, blood pressure, and medical visit status. Group labels will be coded as Group A, B, or C to maintain evaluator blinding. Once the analysis is complete and results are confirmed, evaluator blinding will be lifted—no later than two months after data delivery. Toshiba recruits participants and obtains e-consent. Participants are screened for eligibility and randomized into three groups. Spot urine samples are analyzed by Healthcare Systems Co., Ltd. under contract from Wellmira Inc. Health behavior and awareness surveys are conducted online. Wellmira manages intervention content and data anonymization. Kyoto University conducts analysis in a blinded manner.

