### 3) Measures and Schedule

#### i. Measurement items, methods, and agencies

- a. Salt intake before and after the intervention will be measured by HS, commissioned by Wellmira Inc., using spot urine tests. Sodium, creatinine, and potassium excretion will be analyzed. Kyoto University will estimate daily salt intake using the INTERSALT formula adjusted for BMI and age. If samples are not submitted by the deadline, Wellmira will follow up with participants.
- b. Behavior change intentions and healthcare utilization before and after the intervention will be assessed via online surveys based on the transtheoretical model. The question will be “What do you think about improving eating habits?” with options: 1 = “Not interested”, 2 = “Need to improve but cannot do it”, 3 = “Want to do it now”, 4 = “Have been implementing improvements for less than 6 months”, or 5 = “Have been implementing improvements for more than 6 months”. Medical visit status will be surveyed similarly. If responses are not submitted on time, Wellmira will follow up. Pre-intervention surveys will be administered by HS, post-intervention by Wellmira.
- c. Post-intervention age, weight, and systolic/diastolic BP will be collected via online survey by Wellmira. If values differ greatly from baseline health check data, Wellmira will contact participants for confirmation. Reminders will be sent for unsubmitted surveys.
- d. Pre-intervention age, sex, height, weight, and blood pressure will be provided by Toshiba

based on 2023 health check data.

ii. Measurement Schedule

| Date                                   | Events                                                                                                                                                                                                                     |
|----------------------------------------|----------------------------------------------------------------------------------------------------------------------------------------------------------------------------------------------------------------------------|
| March 29, 2024-July 3, 2024            | Obtain consent for participation                                                                                                                                                                                           |

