
221 10. Sample and Data Storage and Disposal

222 1) Storage Duration

223 Samples and data will be stored for 10 years after the study concludes, in accordance with  
224 institutional policies.

226 2) Storage Method

227 i. Toshiba

228 Data will be stored on electronic media, in a locked safe installed in a security-enhanced  
229 area of the company equipped with surveillance cameras. Entry to this area is restricted  
230 by biometric authentication and electronic locks to prevent access by unauthorized  
231 individuals. For analysis purposes, a dedicated analysis computer located within this  
232 secure area will be used in a completely offline (disconnected) state. The analysis  
233 computer will be periodically connected to internal servers protected by the company's  
234 firewall to update antivirus software and operating system patches, managed by the  
235 administrator.

237 ii. Wellmira

238 Personal data will be stored on Wellmira's dedicated internal server for personal  
239 information. Access to this server is strictly limited to the designated personal  
240 information manager and a small number of authorized personnel within the company.  
241 The server is located in a security room equipped with surveillance cameras and  
242 electronic locks to control entry and exit, managed under the supervision of the personal  
243 information manager. The server is also regularly connected to internal management  
244 servers within the firewall for antivirus and OS updates. To respond to inquiries, the  
245 research-specific email addresses, group allocation information (intervention, control  
246 group, app-only group), and participant IDs are temporarily stored. Additionally, the  
247 post-trial survey data, which is collected via Google Forms, will be temporarily stored  
248 on Google Workspace cloud storage. After the response deadline, the survey form will  
249 be immediately transferred to Wellmira's secure internal server, and all data will be  
250 permanently deleted from the cloud. Any information received from Toshiba or  
251 Healthcare Systems Co., Ltd. that is encrypted with passwords—whether transported via  
252 hard drive or file transmission systems—will also be transferred to the secure server.  
253 Urine samples collected by HS on behalf of Wellmira will not be stored after  
254 measurement and will be immediately discarded.

256 iii. Kyoto University

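### Wellmira, which knows allocation and delivers the intervention, decides at its discretion which post-intervention weight and blood pressure values to query before the coded data reach the blinded analysts

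*Protocol*

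**What the plan says.** **Who knows allocation.** Section 5, 2) Methods: "Toshiba will generate a participant list with IDs, allocation groups, and health check data from 2023", and this list goes to Wellmira. Section 10, 2) ii, adds that Wellmira temporarily holds "research-specific email addresses, group allocation information (intervention, control" and the third arm, together with participant IDs, so that it can answer inquiries. Section 5, 1) claims blinding for participants and for the Kyoto University evaluators, and makes no such claim for Wellmira.

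**Wellmira's position.** It informs the intervention arm of the genotype and runs the app content (section 5, 2). Section 13, 2) makes it a co-investigator and co-author, and section 21 a joint owner of the results.

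**How data reach the analysts.** "HS will report post-intervention urine test results to Wellmira". On surveys, section 5, 3) i, item b states: "Pre-intervention surveys will be administered by HS, post-intervention by Wellmira". "Wellmira manages intervention content and data anonymization", and it supplies the file that Kyoto University analyses, with groups labelled A, B or C.

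**The query rule.** Item c covers self-reported post-intervention age, weight, and systolic and diastolic pressure: "If values differ greatly from baseline health check data, Wellmira will contact participants for confirmation". The protocol gives no limit, names no person without access to allocation to raise the query, and mentions no record of the value before confirmation.

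**The concern.** A plausibility check on self-reported data is ordinary practice. Three features of this one combine badly.

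- It is triggered by distance from baseline. Change in blood pressure and BMI is what the secondary outcomes measure, so the check selects on the outcome.
- How large a difference must be is left to judgement.
- The party judging knows each participant's arm and has an interest in the result.

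If large falls are accepted more readily in one arm, or large rises questioned more readily, the confirmed data differ between arms for a reason unrelated to treatment. Recoding the groups afterwards hides the labels from the analysts but does not undo a selection already made. At stake are the comparisons of systolic pressure, diastolic pressure and BMI, and the claim that evaluation was blinded.

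**Working it through.** The protocol attaches no figure to this point, so there is none to reproduce. The check is a trace of the data flow, followed by one illustration.

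**Step 1: which data the query rule reaches**

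| Item (section 5, 3) i) | Collected or measured by | Wellmira's stated action on values | Outcome affected |
|---|---|---|---|
| a. Urine sodium, potassium, creatinine | HS | none; follows up unsubmitted samples | primary |
| b. Behavior-change question, medical visits | HS before, Wellmira after | none; follows up late answers | secondary (intention) |
| c. Post-intervention age, weight, SBP, DBP | Wellmira, by online survey | contacts the participant after a large difference from baseline | SBP, DBP, BMI |

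Only item c carries a query on values.

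**Step 2: the order of events after randomisation**

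1. Wellmira receives IDs, allocation and the 2023 health check values.
2. It delivers the intervention.
3. It collects the post-intervention survey and raises queries under item c.
4. It assembles the file and codes the groups.
5. Kyoto University analyses with coded labels.

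Blinding begins at step 4. The query at step 3 comes before it.

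**Step 3: how often the rule might be used.** The protocol gives no frequency. The baseline is a 2023 health check and the trial ends on 9 December 2024. Even a check on 31 December 2023 precedes that date by 344 days. The later value is self-reported, and pressure is given only if the participant can measure it. Entry required raised pressure at a 2022 or 2023 check, so some regression to the mean is expected. Large differences are therefore plausible in every arm.

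**Step 4: link to the primary outcome.** Kyoto University estimates salt intake with the INTERSALT formula, adjusted for BMI and age. Item a does not say which weight supplies the post-intervention BMI. If it is the self-reported weight, a weight changed on confirmation alters the estimate. If baseline weight is used, this path is closed.

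**Step 5: illustration under assumptions.** Let p be the net excess share of values changed in one arm, and c the mean change, all in one direction. The between-group difference then shifts by p × c.

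- p = 2%, c = 5 mmHg: 0.02 × 5 = 0.1 mmHg
- p = 5%, c = 10 mmHg: 0.05 × 10 = 0.5 mmHg
- p = 10%, c = 20 mmHg: 0.10 × 20 = 2.0 mmHg

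Neither p nor c comes from the protocol. The range shows only how such a bias would scale.

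**The case against.** The strongest reply is that the protocol asks for confirmation only. It gives Wellmira no authority to change, delete or select a value, and any change would be the participant's own answer. The rule makes no distinction by arm. Numeric limits often stand in a data management plan or SAP, and the SAP is not at hand. All of this is correct, and the missing number alone would not be a finding. What remains is fixed in the protocol itself: who raises the queries, what that party knows, and that the trigger is change from baseline. Asking again only those participants whom an unblinded party picks out can alter the data even if every answer is honest.

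A reader might infer more than this, and the protocol does not support it:

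- **That outcome data are edited unblinded.** The text describes contact, not editing.
- **That Wellmira queries urine results.** Its only stated action there is to follow up unsubmitted samples. HS measures the analytes and Kyoto University computes intake.
- **That Wellmira sees all results first.** HS holds the urine results and pre-intervention answers before Wellmira does, and the pre-intervention results precede randomisation. Wellmira comes first only relative to the analysts.
- **That a single data route by itself weakens the primary result.** If laboratory values are passed on unchanged, they are the same by either route. A source record also exists outside Wellmira: "HS will report post-intervention urine test results to Wellmira and notify participants of their own pre- and post-test results".

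It is also fair to object that the remedy needs new procedures, including separated access at Wellmira and a de-identified laboratory file. That cost is real but modest.

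**Conclusion.** The point holds in a limited form. An unblinded party with an interest in the result applies a discretionary query, triggered by change in the measures that make up the secondary outcomes, before the analysts' blinding takes effect. Systolic pressure, diastolic pressure and BMI are directly exposed. The primary outcome is exposed only if self-reported post-intervention weight enters the BMI term.

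No bias is shown, and its size cannot be computed from the protocol. The 0.1 to 2.0 mmHg range rests wholly on assumed shares and changes and concerns blood pressure only. The conclusion assumes that no unseen document keeps allocation from the staff who raise queries. Nothing in the protocol suggests misconduct.

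**What to change.** 1. **Section 5, 3) i, item c.** Set numeric query limits for weight and for systolic and diastolic pressure. Apply them identically in all arms, from a list that does not show allocation. Send Kyoto University both the original and the confirmed value, with a query log. Add a sensitivity analysis of blood pressure and BMI on the original values.
2. **Section 5, 2).** Have HS also send a de-identified urine file, keyed by study ID, directly to Kyoto University, to be reconciled with the file from Wellmira. Section 8, 5) already requires Kyoto University to delete data it has received for participants who withdraw, so that rule can cover the second file. If collection is complete, the reconciliation is still useful.

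The cost is one extra encrypted transfer with a de-identified extract, separated access to allocation for query staff at Wellmira, and one extra sensitivity analysis. HS already holds the study IDs and urine results, and section 8, 3) already provides for encrypted transfer.

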#### 4) Sample Size and Rationale

A total of 451 participants are planned, with 208 allocated to the intervention group, 208 to the control group, and 35 to the app-only group. Celis-Morales et al. (2017) reported a 0.74g reduction in salt intake after 3 months in the intervention group compared to the control group. In addition, a systematic review by Huang et al. (2016) found that the standard deviation (SD) of estimated salt intake using the INTERSALT method from spot urine samples ranged from approximately 2.0 to 2.2g. Assuming an effect size of 0.74g and an SD of 2.2g, with a significance level of 5% and power of 90%, the required sample size for the primary comparison between the intervention group and the control group is 187 participants per group, totaling 374 participants. For the supplementary analysis comparing the intervention group and the app-only group, a sample size of 31 is required to obtain a 95% confidence interval of  $\pm 0.74$ g, assuming the same SD and significance level. Adding these together results in 405 participants, and allowing for a maximum dropout rate of 10%, the final sample size is set at 451 participants.

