### 5. Methods and Scientific Validity

#### 1) Study Design

This study is a three-arm parallel-group randomized controlled trial. Participants in the intervention group will be informed at the beginning of the trial that they carry a salt sensitivity genotype and will be asked to record their dietary intake using the *CALOmama PLUS* app. They will also receive weekly columns and quizzes related to salt reduction via the app. The control group will receive no intervention. The app-only group will be asked to record their dietary intake using the *CALOmama PLUS* app, but they will not be informed of their genetic information, nor will they receive any salt reduction content. Of the 451 study participants, 208 will be randomly allocated to the intervention group, 208 to the control group, and 35 to the app-only group. Over 600 individuals have already applied, ensuring the target sample size is attainable. Participants will not be informed of their group allocation (participant blinding). Evaluators at Kyoto University will also be blinded to group assignments (evaluator blinding).

|                                 | Control group
(n = 208) | App-only group
(n = 35) | Intervention group
(n = 208) |
|---------------------------------|----------------------------|----------------------------|---------------------------------|
| Genetic profile                 | ×                          | ×                          | ✓                               |
| CALOmama PLUS app use    | ×                          | ✓                          | ✓                               |
| Information on sodium reduction | ×                          | ×                          | ✓                               |

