| July 30, 2024                          | Submit spot urine and complete survey (approx. 1 minute)                                                                                                                                                                   |
| September 10, 2024
(start of trial) | Intervention group: Notified of salt-sensitive genotype and asked to log meals in CALOmama PLUS for 3 months
Control group: No action
App-only group: Asked to log meals in CALOmama PLUS for 3 months |
| December 9, 2024
(end of trial)     | All participants: Submit spot urine and complete survey (approx. 1 minute)
Control and app-only groups: Notified of salt-sensitive genotype
Control group: May begin using CALOmama PLUS if desired           |

4) Analysis Overview

The primary analysis will compare the intervention group to the control group. A supplementary analysis will compare the intervention group to the app-only group to assess the effect of *CALOmama PLUS* use alone.

- i. Primary Outcome: Sodium intake
- ii. Secondary Outcomes: Behavior change intentions, systolic and diastolic blood pressure, BMI
- iii. Main Analytical Method: Analysis of covariance

6. Study Duration

1) Recruitment Period

From the date of institutional approval to July 3, 2024

2) Intervention Period

Three months from the date of recruitment

3) Study Period

From the date of institutional approval to March 31, 2026

7. Informed Consent

Toshiba Corporation will set up a dedicated website accessible only to its employees, through which it will provide explanations about the study and obtain electronic signatures on the informed consent form from interested participants. The company will offer opportunities for participants to ask questions about the study content and will provide adequate answers. After obtaining informed consent, participants will have continued access to the consent materials. Printed documents will be provided upon request.

8. Handling of Personal Information

1) Types of Personal Information Collected

Personal information

2) Creation Period and Method

In July 2024, when participants are finalized, Toshiba will generate an ID list electronically. This list will be managed and stored by individuals within Toshiba who are not involved in this study, and study personnel will not have access to it.

3) Types of Personal Information Retained and Security Measures

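### The supplementary comparison of intervention with app-only cannot measure the effect of the app alone, because both arms use the app

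*Protocol*

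**What the plan says.** Section 5 of the Protocol, under Analysis Overview, names two comparisons. The first is the primary one: "The primary analysis will compare the intervention group to the control group". The second is: "A supplementary analysis will compare the intervention group to the app-only group to assess the effect of *CALOmama PLUS* use alone". The sample size section (section 4) names the same pair of arms when it sizes the third arm: "For the supplementary analysis comparing the intervention group and the app-only group".

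The content of the arms is set out under Study Design in section 5:

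- **Intervention:** participants are told that they "carry a salt sensitivity genotype and will be asked to record their dietary intake using the *CALOmama PLUS* app". In addition, "They will also receive weekly columns and quizzes related to salt reduction via the app".
- **App-only:** "The app-only group will be asked to record their dietary intake using the *CALOmama PLUS* app". The same sentence then withholds the other two components from this arm: "but they will not be informed of their genetic information, nor will they receive any salt reduction content".
- **Control:** "The control group will receive no intervention".

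The table in that section, the Methods text and the measurement schedule agree with this. No section of the Protocol plans a comparison of app-only with control.

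**The concern.** The stated purpose and the stated contrast do not match. A difference between two arms estimates the effect of what differs between them, and app use does not differ between intervention and app-only. Followed as written, the trial would report the added effect of genotype notification and salt content under the name of the app's effect.

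Which component does the work is part of the trial's rationale. The Background section says that in one earlier trial genetic information added no significant effect to personalised advice, and it calls the evidence inconclusive. A mislabelled contrast would credit or discredit the wrong component. A large difference would be read as evidence that the app works by itself, when it would show that the app needed the additions. A difference near zero would be read as evidence that the app does nothing, when it would be compatible with the app doing everything.

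**Working it through.** No stated figure underlies this point. The check is which effect each contrast identifies.

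**Arm contents** (Study Design text and table):

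| Component | Control (C) | App-only (A) | Intervention (I) |
|---|---|---|---|
| App use | no | yes | yes |
| Genotype notification | no | no | yes |
| Salt-reduction content | no | no | yes |

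**Differences between arms:**

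- I − C = app + notification + content, the whole package (primary, planned).
- I − A = notification + content, given app use (supplementary, planned, labelled as the app alone).
- A − C = app use alone (not planned).

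The app effect could be derived as (I − C) − (I − A), but that is simply A − C.

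**Size of the mislabelling.** Assume additive effects and a total I − C of 0.74 g, the effect used in the sample size section. Then I − A = 0.74 − (app effect):

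| True app effect (g) | I − A estimates (g) |
|---|---|
| 0 | 0.74 |
| 0.20 | 0.54 |
| 0.37 | 0.37 |
| 0.74 | 0 |

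The estimate falls as the app effect rises. The two agree only when the app accounts for exactly half of the total. The splits are illustrations of direction; the Protocol gives no figure for the components.

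**Precision of the contrast that answers the question.** Inputs are the SD of 2.2 g and the group sizes in the sample size section. The 95% half-width, unadjusted and with a common SD, is 1.96 × SD × √(1/n₁ + 1/n₂).

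- As randomised (208 and 35): 1.96 × 2.2 × √(1/208 + 1/35) = 0.79 g.
- At the sizes before the dropout allowance (187 and 31): 1.96 × 2.2 × √(1/187 + 1/31) = 0.84 g.

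Intervention and control are the same size, so these half-widths apply equally to I − A and A − C. Both are wider than the ±0.74 g that the sample size section gives for this comparison. That is a separate matter and does not bear on which effect is estimated.

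**The case against.** The case on the other side accepts the mismatch and disputes its weight.

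- **The analysis is supplementary.** It is sized by interval width rather than power, and the primary contrast, outcome, allocation and 187 per group do not depend on it. This stands and limits the consequence.
- **The arms are clearly described.** A careful reader could see what the contrast contains. That lessens the harm, but the label is still wrong and would carry into the report.
- **The comparison is too imprecise to settle any component question.** Half-widths of 0.79 to 0.84 g exceed the whole assumed effect of 0.74 g, so the trial could hardly separate the splits in the illustration. This also stands, though covariance adjustment may narrow the interval by an amount the Protocol gives no basis to quantify. It argues for cautious claims. It does not make the label correct, since the estimate would still be reported as the effect of the wrong component.
- **The contrast may be deliberate and only its description wrong.** The same pair is named in two sections, and the intention may have been to assess the package net of app use. That is plausible, and the contrast is worth keeping. The text does not say so, however, and the reading calls for the purpose clause to be rewritten.
- **Adding app-only versus control, or stating that notification and content cannot be separated, goes beyond the defect.** In part this is fair. The extra contrast is needed only if the effect of the app alone is really wanted, as the Protocol now says it is. The statement on separability is a useful clarification, since no section claims to separate the two.

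**Conclusion.** The concern holds. The Protocol assigns to intervention versus app-only an effect that this contrast cannot estimate, and it omits the contrast that can. This follows from the arm descriptions alone and needs no numerical assumption. It is not a detail left to an analysis plan, because the Protocol fixes both the contrast and its purpose: a plan that followed it would inherit the error, and one that departed from it would contradict it.

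Under additivity and a total of 0.74 g, the error in what is reported as the app effect could be as large as 0.74 g in either direction, at the two extremes of the split. The primary comparison and its sample size are unaffected.

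**What to change.** In section 5, Analysis Overview, define the supplementary contrasts by what they estimate:

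1. Intervention versus app-only: the added effect of genotype notification together with salt-reduction content, among participants who use the app. Remove the clause that describes this as the effect of the app alone.
2. App-only versus control: the effect of app use alone. Add this if that question is to be kept.

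It would also help to say that the design does not separate genotype notification from the salt content, and to describe both supplementary contrasts as estimates with wide intervals. The supplementary comparison in the sample size section should be described in the same terms.

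The cost is a few sentences and one more contrast in the analysis of covariance, on data already collected. No extra participants are needed, and precision is the same as for the contrast already planned.
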